### Assessments

#### Questionnaires

The pediatric asthma quality of life questionnaire (PAQLq) [25] will be used. It is composed of 23 questions divided into three domains: physical activity limitations (5 questions), symptoms (10 questions) and emotions (8 questions). The responses will be measured using a 7-point scale, according to which 1 indicates the maximum loss and 7 indicates no loss.

The asthma control questionnaire (ACT or C-ACT) will be applied according to the patient's age [26] to determine whether asthma is controlled. The ACT consists of five questions. The scores of each question range between 1 and 5 points. The questionnaire minimum score is 5 points and the maximum score is 25 points. The C-ACT, which will be applied to children under 11 years and 12 months, consists of seven questions, four of them answered by the children and three by the parents/guardians, with a minimum score of 0 and maximum of 27.

#### Pulmonary function

Spirometry tests will be performed using ULTIMA CPX equipment (MedGraphics Corporation®, St Paul, MN, USA). The technical procedures, acceptance criteria and reproducibility will be adopted according to recommendations [27]. All patients will perform the maneuvers post bronchodilation (salbutamol 400 μcg). The following variables will be recorded: forced vital capacity (FVC), forced expiratory volume at the first second (FEV_1_), FEV_1_/FVC ratio and forced expiratory flow (FEF25-75) [28].

#### Cardiopulmonary exercise testing

The exercise test will be performed in an electromagnetic braking cycle ergometer (Corival®, LODE BV Medical Technology, Groningen, Netherlands) connected to a system composed of gas exchange and ventilatory variables being analyzed breath by breath (Breeze CardiO_2_ System® microcomputer; Medical Graphics Corporation-MGC, St Paul, MN, USA). After 2 minutes of freewheel load, the load will be increased (5 to 20 watts/minute) and the test will be limited between 8 and 12 minutes [29, 30]. The following measurements will be analyzed: oxygen consumption (VO_2_, mL min^−1^) and carbon dioxide production (VCO_2_, mL.min), minute ventilation (V_E_, L/minute), tidal volume (TV) (mL), respiratory rate (f) (respirations/minute), and ventilatory equivalents for O_2_ and CO_2_ (V_E_/VO_2_, V_E_/VCO_2_). The heart rate (HR), pulse oxyhemoglobin saturation (SpO_2_) will be continuously recorded. Blood pressure (BP) will be measured every 2 minutes of exercise. Dyspnea (Borg D) and lower limb fatigue (Borg LL) perception scores will be assessed by using the modified Borg scale [31], with the patient at rest and immediately after the exercise cessation. The test will be interrupted by the child or adolescent due to intolerable dyspnoea and/or fatigue making it impossible to progress the workload. On the other hand, the test will be stopped if SpO_2_ is ≤82 %, or if patients have cardiac arrhythmias or abnormal blood pressure response.

#### Incremental shuttle walking test (ISWT)

The ISWT will be held in a 10-m-long corridor according to the original description [10]. It is a test externally cadenced by an audible signal, in which the speed increases every minute ranging from 1.79 to 10.2 Km/h. The test comes to the end when the patient is not able to reach the cone two consecutive times, or the patient needs to stop the test due to fatigue or breathlessness, or SpO_2_ falls below 82 %. The tests will be performed twice on the same day, with a 30-minute break between them. Heart rate, blood pressure, and Borg fatigue and Borg dyspnea will be evaluated at the beginning and at the end of the test. The total test time and the distance walked by the patient will be recorded at the end of the test.

#### Physical activity in daily life

Each patient will be monitored by an ActiGraph accelerometer (GT3X) throughout seven consecutive days [32]. The accelerometer will be firmly placed on the patient’s hip (pelvic girdle), and it will be removed just for sleeping, bathing and swimming. Each individual or his/her guardian will be given a form for the daily descriptions of unusual activities performed while using the device. The form must be completed at the end of the day. The number of steps will be recorded for analysis.

#### Skeletal muscle function assessment

The maximum isometric voluntary contraction (MIVC) of the quadriceps femoris (QF) muscle will be obtained by having the individuals sit on a leg extension machine (Carci®, São Paulo, Brazil) with their knees positioned at 60 ° flexion. An inelastic cable connected to a load cell and adapted to an anklet (EMG System model EMG800C, São José dos Campos, Brazil) will be positioned perpendicular to the non-dominant lower limb. This cell will capture the muscle tension developed during knee extension MIVC and it will record the force (Kgf).

The MIVC of the biceps brachii (BB) muscle will be obtained by having the individuals sit on a chair. The same equipment will be connected to a load cell and it will be positioned perpendicular to the non-dominant upper limb. This cell will capture the muscle tension developed during the MIVC of elbow flexion and record it on the computer.

Three replicates will be held for 5 seconds, with a 1-minute rest interval between all the measures [33]. The greatest value of these three contractions of QF and BB will be considered as the MIVC.

After a resting period of five minutes, the isometric endurance test (IET) of the QF will be evaluated by the isometric endurance time at 60 % of the MIVC until the limit of tolerance (Tlim). The isometric endurance test will be finished when a 10 % drop of the produced force occurs. The same procedure will be used to verify the endurance of the IET by BB. All measurements will be performed with visual feedback on the computer screen. Dyspnea and leg fatigue will be evaluated before and immediately after the test by the modified Borg scale. This test will take approximately 15 minutes.

#### Surface electromyography (*s*EMG)

The surface electromyographic (sEMG) will be recorded in the dominant upper and lower limb. Active bipolar surface electrodes will be positioned in the belly of the evaluated muscles (RF and BB) as previously described [34]. The *s*EMG (EMG System, model EMG800C, São José dos Campos, Brazil) will be recorded using a 4-channel device (EMG System do Brazil Ltda®), with a band pass filter with cutoff frequencies of 20 to 500 Hz, an amplifier gain of 1000, and a common rejection mode ratio >100 dB. All data will be acquired and processed using a 12-bit analog-to-digital converter, with a sampling frequency of 2 kHz. The obtained signal will be amplified and converted to digital format for data recording and analysis.

The sEMG signal will be divided into 1-second windows and the root mean square (RMS) and median frequency (MDF) of the power spectrum will be calculated for each window. Five consecutive values over RMS time and MDF will be averaged to obtain mean values corresponding to 0, 25, 50, 75, and 100 % of the endurance time. All EMG signals will be processed performing specific routines carried out in the Matlab program, R2010b (The MathWorks Inc., Natick, MA, USA).

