**Method:**

This is a study protocol of randomized controlled trial in asthmatic patients between 6 to 18 years old. The assessments will be conducted in three different days and will be performed at the beginning and at the end of the protocol. First visit: quality of life questionnaire, asthma control questionnaire, pre- and post-bronchodilator spirometry (400 μcg salbutamol), inflammatory assessment (blood collection), and cardiopulmonary exercise test on a cycle ergometer to determine aerobic capacity. Second visit: assessment of strength and endurance of the quadriceps femoris and biceps brachii muscles with concomitant electromyography to assess peripheral muscle strength. Third visit: incremental shuttle walk test (ISWT) and accelerometer to evaluate functional capacity and physical activity in daily life during 7 days. Then, the volunteers will be randomized to receive pulmonary rehabilitation program (intervention group) or chest physiotherapy + stretching exercises (control group). Both groups will have a supervised session, twice a week, each session will have 60 minutes duration, with minimum interval of 24 hours, for a period of 8 weeks. Intervention group: aerobic training (35 minutes) intensity between 60 to 80 % of the maximum workload of cardiopulmonary exercise testing or of ISWT; strength muscle training will be applied to the quadriceps femoris, biceps brachii and deltoid muscles (intensity: 40 to 70 % of maximal repetition, 3 x 8 repetition); finally the oral high-frequency oscillation device (Flutter®) will be used for 5 minutes. The control group: oral high-frequency oscillation device (Flutter®) for 10 minutes followed by the stretching of upper and lower limbs for 40 minutes. It is expected to observe the improvement in aerobic capacity, physical activity in daily life, muscle strength and quality of life of patients in the intervention group, and reduction in inflammatory markers.

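### The load cell is placed on the non-dominant leg and arm but the EMG electrodes on the dominant ones, so the EMG-by-endurance-time analysis would not describe the tested muscle

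*Protocol article*

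**What the plan says.** **Force.** Under Skeletal muscle function assessment, the cable and load cell for the quadriceps contraction "will be positioned perpendicular to the non-dominant lower limb". For the biceps the same equipment is used, and "it will be positioned perpendicular to the non-dominant upper limb".

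**Endurance.** The same section measures the quadriceps by "isometric endurance time at 60 % of the MIVC until the limit of tolerance (Tlim". It stops the test on a force criterion: "The isometric endurance test will be finished when a 10 % drop of the produced force occurs". The biceps follows the same procedure. The limb is not named again for this test.

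**EMG.** Under Surface electromyography (sEMG), the signal "will be recorded in the dominant upper and lower limb". The electrode sites are described thus: "Active bipolar surface electrodes will be positioned in the belly of the evaluated muscles (RF and BB". RMS and median frequency are averaged to give "mean values corresponding to 0, 25, 50, 75, and 100 % of the endurance time".

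**Link between them.** The Method part of the abstract describes the second visit as strength and endurance assessment "with concomitant electromyography to assess peripheral muscle strength". The visit list under Protocol also pairs the two at Visit 2. The Statistical analysis section analyses the EMG variables by group, percentage of endurance time and pre/post assessment in a three-way repeated measures ANOVA.

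**The concern.** EMG amplitude and median frequency plotted against percentage of endurance time are informative about fatigue only when the signal comes from the muscle sustaining the contraction. Here one section puts the force transducer on one side of the body and the next puts the electrodes on the other.

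If an assessor follows both sections to the letter, the time axis comes from one limb and the signal from its opposite. The ANOVA would still run and produce p-values, but its endurance-time effect and its interactions with group and with pre/post assessment would not describe the tested muscle. If assessors instead resolve the conflict for themselves, the recorded limb could differ between children, or between the two assessments of one child. In that case a pre/post change would mix training with a change of side.

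The Background says that the investigators know of no study using EMG to assess peripheral muscle strength and endurance in asthmatic children. It is one of several gaps that they list, so this component has a stated purpose. The Trial status section says that recruitment is under way, and a pre-training recording from the wrong limb cannot be retaken once training has begun.

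**Working it through.** No figure in the plan is in dispute, so the check compares the texts.

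**Step 1: limb named for each measurement.**

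| Measurement | Section | Limb |
|---|---|---|
| Quadriceps maximal force | Skeletal muscle function assessment | Non-dominant (stated) |
| Biceps maximal force | Skeletal muscle function assessment | Non-dominant (stated) |
| Endurance test, both muscles | Skeletal muscle function assessment | Not named |
| EMG, upper and lower limb | Surface electromyography (sEMG) | Dominant (stated) |

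For maximal force against EMG the conflict is explicit. For the endurance test the limb has to be inferred.

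**Step 2: limb for the endurance test.** Two features tie it to the load-cell set-up. The target is 60 % of the maximal contraction, which is obtained on the non-dominant limb. The test ends on a 10 % fall in force, which requires a force reading. The only load-cell placement described is on the non-dominant side, so that is the natural reading.

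**Step 3: does the plan need one limb?** Three statements say so. The abstract makes the EMG concomitant with the strength and endurance tests. The electrodes go on the evaluated muscles. The EMG values are indexed to endurance time, both under Surface electromyography and in the ANOVA.

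**Step 4: can the sections be reconciled as they stand?** The article describes no bilateral contraction, no second test on the dominant limb, and no reason to record the opposite side. The possible readings are:

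- *Endurance on the non-dominant limb (Step 2).* EMG comes from the limb opposite the one tested.
- *Endurance on the dominant limb.* EMG then matches the endurance test, but the 60 % target is taken from the other limb's maximum, so force and endurance no longer match.
- *One limb word is a slip and staff use one limb throughout.* No data are harmed, but the text is wrong in one of the two sections.
- *Staff resolve it differently.* Side varies between or within children.

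No reading leaves both sections correct and force, endurance and EMG on one limb.

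**Step 5: extent.** The EMG values planned per child are 2 muscles x 2 variables (RMS, median frequency) x 5 points of endurance time x 2 assessments = 40. On the literal reading all 40 are affected. On the slip reading none is.

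**Step 6: what is untouched.** Under Outcomes, the primary outcome is physical capacity by CPET and ISWT. The sample size rests on shuttle levels and CPET load. Strength is read from the load cell. None of these uses the EMG signal.

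**The case against.** The strongest reply is that this is a one-word slip and not a design. The phrase about the evaluated muscles, the indexing to endurance time and the word concomitant all point to a single limb, so staff may well be recording the right one. That is likely, and it means that the loss of all EMG values is a worst case for which the article gives no evidence. But the article does not show which word is wrong, and both statements are explicit. This is therefore not a detail left to a fuller protocol.

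A second reply is that little depends on it. RMS and median frequency are not named under Outcomes, and strength comes from the load cell. This limits the consequence and is accepted. It does not remove the point, because the EMG variables have their own three-way ANOVA.

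Two stronger readings are tempting, and the document does not support them:

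- A reader might infer that the EMG would be taken from a limb that is not contracting. The article never says that the other limb rests. The supportable statement is that the signal would not come from the muscle whose force and endurance time are recorded.
- A reader might infer that the non-dominant limb is the right one because it is named twice. Both mentions are in the same section, and if the slip is there, copying that word across would put the error in both places.

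**Conclusion.** The point holds as an internal contradiction between the Skeletal muscle function assessment and Surface electromyography sections. Followed literally, RMS and median frequency over endurance time would not come from the tested muscle, and the three-way ANOVA could not be interpreted as that muscle's fatigue or its change with training. Analysis cannot repair a recording from the wrong limb.

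The damage is confined to the EMG variables. CPET, ISWT, the sample size and load-cell strength are unaffected.

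The conclusion rests on one inference, that the endurance test uses the load-cell limb. If that were wrong, the mismatch would move to the 60 % target but would not disappear. How much data is affected, from none to all 40 values per child, depends on what staff have actually done, which the document does not show.

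**What to change.** 1. Check the assessment records to establish which limb has been used for maximal force, for endurance and for EMG in the children assessed so far.
2. Name that one limb in both sections, for load cell, endurance test and electrodes alike, and state that it is the same at the pre and post assessments.
3. Restrict the EMG-by-endurance-time ANOVA to recordings taken from the tested limb. Decide inclusion from the limb record alone, without regard to group or to the EMG values.

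The cost is a short correction to the text and a review of existing records. Some EMG recordings may have to be excluded if they came from the other limb, or if the side cannot be established. No other outcome or calculation needs to change.

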### Intervention group

The intervention group will have a supervised rehabilitation program held twice a week. Each session will be 60 minutes in duration, with a minimum interval of 24 hours, for a period of 8 weeks. Each session will consist of three parts: aerobic training, strength muscle training, and chest physiotherapy. The aerobic training will be held for 35 minutes (10 minutes of warm up, 20 minutes on target load, and 5 minutes of cooling down) with an initial intensity of 60 % of the maximum load obtained in the maximal cardiopulmonary exercise testing or in the ISWT. The intensity will be gradually increased up to 80 %, so that fatigue or dyspnea values are kept between 4 and 6, according to the modified Borg scale [31]. When necessary, supplemental oxygen will be supplied during training to keep oxygen saturation greater than 92 %. Strength muscle training will be applied to the quadriceps femoris, biceps brachii, and deltoid muscles for 15 minutes. The intensity will be 40 to 70 % of maximal repetition (1 MR) in three sets of eight repetitions. Finally, for chest physiotherapy, the oral high-frequency oscillation device (Flutter®) will be used for 5 minutes. The volunteers in this group will receive a 200-μcg bronchodilator before starting the session each day.

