### Control group

The control group will have chest physiotherapy and stretching exercises twice a week. Each session will be 60 minutes, with a minimum interval of 24 hours, for a period of 8 weeks. For each session, the oral high-frequency oscillation device (Flutter®) will be used for 10 minutes, 5 minutes in each lateral decubitus position, followed by stretching of the upper and lower limbs for 40 minutes. All exercises will be active, performed in sitting and lying positions without increasing the heart rate. The remaining 10 minutes will be used to discuss doubts about the disease and the use of the booklet.

Both groups will be oriented about the disease (proper use of medication, use of peak flow, triggering factors for crisis). On the date of the initial evaluation, they will take home a booklet with the main information about the given guidelines. All volunteers will be reevaluated after 8 weeks, when the same initial assessments will be performed again.

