### Statistical analysis

The sample size was based on the run shuttle walk test levels and on the maximum load achieved in CPET [14]. Considering the stages of the shuttle, and assuming an alpha risk of 5 % and beta risk of 80 %, standard deviation of 1.6, and a difference in magnitude of 2.0 levels before and after the pulmonary rehabilitation program [14], the sample size needed was 27 patients in each group. Considering the load (W) achieved in the cardiopulmonary exercise testing, with a −3 ± 2 W difference pre- and post-intervention in the control group, and of 16 ± 7 [20] in the intervention group, with an alpha risk of 5 % and a beta risk of 95 %, the sample size needed was 10 patients in each group. Therefore, considering potential losses, 30 asthmatic patients will be recruited for each group, requiring a total of 66 volunteers.

The data normality will be analyzed using the Kolmogorov-Smirnov test. Parametric data will be represented as means (SD) and nonparametric data as medians (IQR (25th−75th percentiles ). Comparisons between groups and time (pre- and post-rehabilitation) will be analyzed by two-way analysis of variance (ANOVA), with the Bonferroni test post hoc, or by the Kruskal Wallis test, depending on the data adherence or non-adherence to the Gaussian curve. Correlation between variables will be analyzed by Pearson or Spearman correlation according to the data distribution. Three-way repeated measures ANOVA group vs endurance (0–100 % endurance time, 25 % increments time) vs time (pre- and post-) will be used to assess the dependency of the EMG variables and will followed by post hoc Student–Newman–Keuls pairwise comparisons, when appropriate. The value of *P* <0.05 will be set as significant. SPSS version 13 (Chicago, IL, USA) will be the statistical software used in the study.

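### The EMG plan compares RMS across visits and arms with no within-session reference step, so a strength gain in the trained arm could be misread as changed activation or fatigue

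*Protocol article*

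**What the plan says.** The surface EMG section of the protocol article describes the processing in detail: filter band, gain, sampling rate and 1-second windows. Then "the root mean square (RMS) and median frequency (MDF) of the power spectrum will be calculated for each window", and five consecutive values "will be averaged to obtain mean values corresponding to 0, 25, 50, 75, and 100 % of the endurance time". The Statistical analysis section takes these into a three-way repeated measures ANOVA (group, endurance point, pre/post) that "will be used to assess the dependency of the EMG variables". No step expresses RMS relative to a maximal contraction or to the start of the hold.

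The other relevant statements are:

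- **Load of the hold** (Skeletal muscle function assessment): "isometric endurance time at 60 % of the MIVC until the limit of tolerance (Tlim").
- **Maximal contractions** (same section): three 5-second efforts per muscle. "The greatest value of these three contractions of QF and BB will be considered as the MIVC". Only force is said to be taken from them.
- **Repeat at 8 weeks** (Control group): "All volunteers will be reevaluated after 8 weeks, when the same initial assessments will be performed again".
- **Training** (Intervention group): "Strength muscle training will be applied to the quadriceps femoris, biceps brachii, and deltoid muscles for 15 minutes". The control arm has Flutter and stretching.
- **Limb**: the load cell is attached to the non-dominant leg and arm. EMG is recorded on the dominant leg and arm.
- **Outcomes section**: EMG is not listed. Peripheral muscle strength is a secondary outcome, and the abstract places EMG alongside the strength and endurance testing.

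**The concern.** The absolute level of surface EMG depends on how hard the muscle is working and on the recording conditions of that session. A comparison of levels across visits 8 weeks apart, and across children aged 6 to 18, needs something to put sessions on a common scale. The described chain has nothing of this kind.

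The design makes this matter for one reason in particular. The hold is set relative to the child's own maximum. If training raises that maximum and the target is reset, the trained child holds a higher absolute force at the second visit, and RMS rises with it at every point of the hold. The group-by-time term for RMS then repeats the strength gain that the load cell has already measured. A reader could take it as evidence that training changed muscle activation or fatigue, when activation relative to maximum was the same as before.

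**Working it through.** The article states no figure on this point, so there is nothing to reproduce. The check is of the mechanism.

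**Inputs from the article.** Hold at 60 % of MIVC; assessments repeated at 8 weeks; quadriceps and biceps strength-trained in the intervention arm only; significance at P < 0.05 (taken as two-sided); 27 per arm, from the shuttle-based sample size.

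**Assumptions, not in the article.** RMS proportional to force; strength gain of 0 to 30 % in the intervention arm and none in the control arm; re-siting coefficient of variation (CV) of 10 to 30 % per session, the same in both arms; residual CV of 10 % per recording; force and EMG from the same limb; target reset to the new MIVC.

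**Step 1, force.** Post/pre ratio of force in the hold = (0.6 × MIVC post)/(0.6 × MIVC pre) = MIVC post/MIVC pre. A gain of 10, 20 or 30 % gives a ratio of 1.10, 1.20 or 1.30, and the same ratio in absolute RMS.

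**Step 2, noise.** On the log scale each variance is ln(1 + CV²): 0.0100 for a CV of 10 %, 0.0392 for 20 %, 0.0862 for 30 %.

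- Unreferenced RMS: SD of the pre-post change = √[2 × (re-siting variance + residual variance)] = 0.20, 0.31 and 0.44 at re-siting CVs of 10, 20 and 30 %.
- RMS divided by the same session's MIVC RMS: the re-siting factor cancels and a second residual enters, so SD = √(4 × 0.0100) = 0.20 throughout.

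The reference therefore gains no precision at a re-siting CV of 10 %, and a good deal at 20 to 30 %.

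**Step 3, group-by-time term.** The change in log RMS was simulated for 27 per arm, 10,000 trials per scenario, and compared between arms by a two-sided t test at 5 %. This is the group-by-time contrast at one endurance point, not the full three-way ANOVA. Share of trials significant with unreferenced RMS:

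| Re-siting CV | Gain 0 % | Gain 10 % | Gain 20 % | Gain 30 % |
|---|---|---|---|---|
| 10 % | 4.8 % | 40 % | 90 % | 100 % |
| 20 % | 4.7 % | 20 % | 56 % | 85 % |
| 30 % | 5.3 % | 12 % | 33 % | 58 % |

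Hand check at CV 20 %, gain 20 %: standard error = 0.314 × √(2/27) = 0.085; ln 1.20 = 0.182; ratio 2.14; approximate power Φ(2.14 − 1.96) = 57 %, against 56 % simulated.

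In the gain 0 % column, re-siting alone leaves the error rate at about 5 % and the between-arm difference at about zero. With RMS divided by the same session's MIVC RMS, the rate is 4.6 to 5.3 % in every scenario.

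**Step 4, what is not affected.** If a session factor k multiplies every RMS value, (k × RMS at 100 %)/(k × RMS at 0 %) is free of k. The relative change within a hold is intact. A scale factor does not move a median frequency either.

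**The case against.** **The article nowhere says that raw values will be analysed.** A reader might infer that it does. The signals are processed by Matlab routines that are not shown, electrode placement follows a cited method, and a journal article condenses the protocol. This stands as far as it goes: the text supports only that a chain described from filter to ANOVA names no reference step. But the article does define the analysed quantity at that level of detail, and followed as written it gives an unreferenced RMS.

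**Re-siting of electrodes is no source of bias here.** A reader might infer that moving the electrodes between visits would itself look like a training effect. The article does not support that. Both randomised arms are re-measured by the same procedure, so without a placement difference by arm the result is noise, as the gain 0 % column shows.

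**The limbs do not match.** As written, the load cell is on the non-dominant limb and the EMG on the dominant one. Taken literally, the recorded muscle is not the one holding 60 % of MIVC, and the force argument does not follow. This stands: the concern presupposes that force and EMG are meant to come from the same limb, and the two sections have to be reconciled in any case.

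**The strength gain is a real effect of training.** This is also right. The fault would lie in the interpretation, not in an effect that does not exist. In addition, the reset of the target is implied by the repeat of all assessments but not stated.

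**The reference recording is not confirmed.** The muscle function section takes only force from the maximal contractions. The abstract speaks of strength and endurance testing with concomitant EMG, which supports EMG being available during those contractions but does not settle it.

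**Conclusion.** The point holds in a limited form and should be corrected. The EMG analysis as described compares RMS across visits and arms without a within-session reference, in a design where the load is relative and one arm trains the tested muscles. A strength gain would pass into the absolute RMS level and could be misread as changed activation or fatigue.

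Under proportionality the size equals the strength gain: 10 to 30 % for the assumed 10 to 30 %. The chance that it reaches significance runs from 12 % to nearly 100 % over the assumed ranges. These figures rest on the stated assumptions about gain, re-siting, proportionality, the reset target and the limb; none is given in the article. The conclusion does not extend to median frequency or to relative RMS change within a hold, and it does not make re-siting a source of bias. EMG is not named as a primary or secondary outcome and strength itself is measured by load cell, so the trial's main conclusions are not at risk.

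**What to change.** 1. Reconcile the muscle function section (non-dominant limb) with the EMG section (dominant limb), so that force and EMG come from the same limb. State whether the 60 % target at 8 weeks is set from the MIVC of that visit.
2. State in the EMG section that RMS in the endurance test is expressed as a percentage of the RMS in the best MIVC contraction of the same muscle, limb and session, before it enters the three-way ANOVA.
3. Use one reference for all patients. A patient-by-patient fallback to the start of the hold would mix scales: under proportionality a hold starts near 60 % of the MIVC reference but at exactly 100 % of its own starting value. If MIVC EMG is not usable as a reference, express RMS relative to the 0 % point for everyone and limit inference to change within the hold. The 0 % point is then constant and carries no information in the ANOVA.

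The cost is small: a few sentences in the article's methods and a short change to the Matlab routine. The maximal contractions are already scheduled, so no visit or contraction is added, provided EMG is recorded during them. The downside is that noise in the MIVC recording enters the denominator; in the check above it offsets the whole precision gain at a re-siting CV of 10 %.
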